### Exclusion criteria (part A)

Unwilling or unable to provide informed consent to take part.Unwilling or unable to comply with study procedures.History of any suspected or confirmed disorder of the immune system that, in the opinion of the investigators, might impair the results of the study.Have a bleeding disorder deemed significant by a member of the study team.Pregnant or breast-feeding females.Group 1 (suspected exposure cohort) only
Known history of Mpox infection.Current symptoms consistent with Mpox.Known exposure to Mpox in the last month.
Group 2 (post-exposure/vaccinated cohort) only
Participants with any ongoing symptoms of Mpox, indicating incomplete recovery.
Group 3 (control cohort only)
Symptoms of Mpox.Known exposure to Mpox in the last month.

**Table 1 Tab1:** Adapted from current WHO case definitions [23]

Clinical criteria for current or past Mpox infection
Epidemiological link to a probable or confirmed case of Mpox-21 days before symptom onset
AND
Unexplained acute rash
AND
One of the following signs or symptoms
• Headache acute onset of fever (> 38.5 °C)
• Lymphadenopathy (swollen lymph nodes)
• Myalgia (muscle pain/body aches)
• Back pain
• Asthenia (profound weakness)
AND
The following common causes of acute rash do not explain the clinical picture: varicella zoster, herpes zoster, measles, herpes simplex, bacterial skin infections, disseminated gonococcus infection, primary or secondary syphilis, chancroid, lymphogranuloma venereum, granuloma inguinale, molluscum contagiosum, allergic reaction (e.g. to plants); and any other locally relevant common causes of papular or vesicular rash.

**Table 2 Tab2:** WHO guidance for laboratory testing for hMPXV virus [24]

Microbiological criteria for current or past Mpox infection
• Nucleic acid amplification testing (NAAT) using real time or conventional hMPXV (preferable) or OPXV PCR assay on either:
o Swabs from the surface of a lesion
o Swabs from exudate from a lesion
o Roofs from more than one lesion
o Lesion crusts
• IgM detection from recent acutely ill patients
• Seroconversion of IgG in paired serum samples, collected at least 21 days apart, with the first serum sample collected during the first week of illness

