## Aims and objectives

### Primary aims and objectives

Part A: The **primary clinical aim** of this study to validate novel immunodiagnostic tools to estimate Mpox sero-prevalence. Primary clinical objectives include:

The collection of biological samples (blood) and clinical metadata from human volunteers at risk of Mpox or who have had past Mpox infection/vaccination.To verify a serum-based ELISA quantitative screening assay, for the detection of anti-Mpox specific IgG antibody, in a Rwandan population with equivalent sensitivity for clade 1a Mpox compared with the clade IIb that it was established for.To validate a prototype blood-based, binary or categorical (sero-positive/sero-negative) point-of-care lateral flow test (POC LFT) for the detection of anti-Mpox specific IgG antibody to inform further development and optimisation.

Part B: The **primary public health aim** is to understand the vaccine cold-chain readiness to deploy Mpox vaccines without detrimental effects on existing WHO EPI and other vaccine supply.

Primary public health objectives include:

To measure the available capacity within sub-networks of the vaccine cold-chain in Rwanda to deploy Mpox vaccines into target populations.To model different modes of vaccine deployment scenarios for most efficient vaccine use and public health impact.

The primary endpoints of this study are

anti-Mpox specific IgG titres as measured by the ELISA,Binary lateral flow test result.Capacity of the VCC in Rwanda as measured by number of vaccine vials stored at max capacity.

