## Recruitment and eligibility

### Recruitment

For Part A, we will use existing operational and health data records in the Rwanda Biomedical Centre (RBC) to identify, contact and invite group-specific members of the population to consider taking part in the study.

We aim to recruit volunteers to one of the following study groups:

Group 1 (suspected exposure cohort): asymptomatic volunteers at risk of Mpox including:
Those who live within or adjacent to, or spend prolonged amounts of time in an epidemiologically identified region of Mpox transmission.Close contacts of those with microbiologically confirmed Mpox.
Group 2 (post-exposure/vaccinated cohort):
Asymptomatic volunteers who have had clinically (Table 1) or microbiologically (Table 2) confirmed Mpox infection within the last one-month (group 2a) or more than one-month ago (group 2b).Those who have received a smallpox/MVA vaccine within the last one-month (group 2c) or more than one-month ago (group 2d).
Group 3 (control cohort): asymptomatic volunteers with no known exposure to Mpox.

For Part B and the primary public health aims of the study, there will be no study volunteer recruitment or collection of personal or sensitive data. The study population here will be vaccine stock inventories in vaccine fridges. These data are already collected and available from the operational records of the Rwanda national health implementation agency, Rwanda Biomedical Centre (project partners).

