### Inclusion criteria (part A)

Healthy males and females aged between ages 5–80 years, who are able and willing to provide informed consent and will comply with the study requirements.Group 1 (suspected exposure cohort) only
Live within or adjacent to an epidemiologically identified region of Mpox transmission.Close contacts of those with microbiologically confirmed Mpox.
Group 2 (post-exposure/vaccinated cohort) only
Previous clinically or microbiologically confirmed Mpox or confirmed previous vaccination with a smallpox/MVA vaccine.Fully recovered from Mpox infection.
Group 3 (control cohort) only:
Asymptomatic with no known exposure to Mpox.

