### Statistical analysis plan

#### Part A

The analyses for this study will be primarily descriptive in purpose (counts/proportions, or geometric mean titre where appropriate) and will not include any hypothesis testing. Comparative analyses (chi-squared/Fisher-exact or paired/unpaired t-test where appropriate) and the presentation of p values will represent post-hoc analyses.

ELISA performance will be assessed by a receiver operating characteristic (ROC) curve and area under the curve analysed to evaluate the ability of the ELISA to distinguish those presumed seropositive (vaccination and infection) from seronegative (no known infection or vaccination). The best cut-off for identifying serostatus will be selected using this method based off the highest sensitivity and specificity.

The Mpox POC LFT performance will be evaluated versus the ELISA and characterised by positive/negative concordance, correlation, test sensitivity, specificity, positive predictive value (PPV), negative predictive value (NPV) and likelihood ratios. The views and perspectives gained from the semi structured interviews will be analysed qualitatively on a small subset of participants (*n* = 30).

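### Clinically diagnosed cases without laboratory proof count as reference positives when the ELISA's AUC, cut-off and sensitivity are set

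*Protocol article*

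**What the plan says.** All references are to the Protocol article.

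- **Entry to groups 2a and 2b** (Recruitment): past infection means "clinically (Table 1) or microbiologically (Table 2) confirmed Mpox infection". Inclusion criteria (part A) repeats the either/or rule: "Previous clinically or microbiologically confirmed Mpox or confirmed previous vaccination with a smallpox/MVA vaccine".
- **Clinical route** (Table 1): four conditions joined by AND. They are "Epidemiological link to a probable or confirmed case of Mpox-21 days before symptom onset", an unexplained acute rash, one further sign or symptom, and no better explanation among a list of other causes of rash. None is a laboratory result, and the linked case may itself be only probable.
- **Microbiological route** (Table 2): NAAT on lesion material, or "IgM detection from recent acutely ill patients", or "Seroconversion of IgG in paired serum samples, collected at least 21 days apart", the first serum coming from the first week of illness.
- **Validation set** (Sample size, Part A): 50 samples each from groups 2b, 2d and 3.
- **Reference classification** (Statistical analysis plan, Part A): the ROC curve is to "distinguish those presumed seropositive (vaccination and infection) from seronegative (no known infection or vaccination", and the cut-off is chosen from that same curve.
- **Index test** (Primary aims and objectives): the endpoint is "anti-Mpox specific IgG titres as measured by the ELISA".
- **Later use** (Laboratory analysis; Study design and setting): the ELISA becomes the reference standard for the lateral flow test and is used for the seroepidemiology stage.

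The article nowhere limits the infection positives to laboratory-confirmed cases or separates them by route. Study design and setting describes the stage 1 samples as having known status; Laboratory analysis says their status is partly known and partly presumed.

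**The concern.** A ROC analysis takes the reference label as truth. A person who met Table 1 but had another rash illness, and was never vaccinated, has no reason to carry mpox antibody. If the ELISA correctly reads that person as negative, the plan scores it as a miss. Apparent sensitivity and AUC fall, and the cut-off may move to accommodate non-cases.

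Group 2b supplies half of the stage 1 positives and all of the stage 1 evidence on sensitivity after infection, including the comparison across clades named in the primary objectives. An error in the cut-off would carry into every lateral flow result judged against the ELISA and into the seroprevalence estimate.

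The entry rule is also looser here than elsewhere. Close contacts in group 1 must be contacts of a microbiologically confirmed case, whereas the group that anchors the assay validation needs no laboratory confirmation at all.

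**Working it through.** The article gives no target sensitivity, interval width or formula for the 50/50/50 validation set, so there is no stated figure to reproduce. The calculations below are illustrations.

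**Inputs from the article:** n = 50 in 2b and n = 50 in 2d.

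**Assumed, because the article gives no figure:** true sensitivity Se = 0.85; false-positive rate FPR = 0.05; share f of 2b that is clinical-only = 0.10 to 0.30; 30% of clinical-only participants are non-cases; 2d is unaffected and also has sensitivity 0.85.

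**1. Clinical-only cases.** The non-case share of 2b is q = 0.3f. Apparent Se in 2b = (1 − q) × 0.85 + q × 0.05. Pooled Se = (apparent Se in 2b + 0.85)/2.

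| f | q | Expected non-cases among 50 | Apparent Se, 2b | Pooled with 2d |
|---|---|---|---|---|
| 0.10 | 0.03 | 1.5 | 0.8245 + 0.0015 = 0.826 | 0.838 |
| 0.20 | 0.06 | 3.0 | 0.7990 + 0.0030 = 0.802 | 0.826 |
| 0.30 | 0.09 | 4.5 | 0.7735 + 0.0045 = 0.778 | 0.814 |

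**2. Other assumptions, same direction.** With Se = 0.95, FPR = 0.05, 25% clinical-only and 30% of those non-cases, q = 0.25 × 0.30 = 0.075. Apparent Se in 2b = 0.925 × 0.95 + 0.075 × 0.05 = 0.883, or 0.916 pooled. With 10–50% clinical-only and 10–50% of those non-cases, apparent Se in 2b runs from 0.941 to 0.725.

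**3. Cut-off and AUC.** If non-cases have the same titres as controls, then at any cut-off the apparent true-positive rate (TPR) in 2b is (1 − q)TPR + q·FPR.

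- The AUC in 2b becomes (1 − q)AUC + 0.5q, which is always lower when the assay discriminates.
- Sensitivity + specificity − 1 in 2b becomes (1 − q)(TPR − FPR). This peaks at the same cut-off as before. Under that criterion the cut-off moves only because the infected count for less relative to the vaccinees in the pooled curve, because non-cases differ from controls, or by chance in a small sample.
- Other readings of the plan's rule, such as the ROC point nearest the ideal corner, do not share this property.

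The loss of apparent sensitivity and AUC therefore follows directly from misclassification. A shift in the cut-off is possible but not certain.

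**4. Serologically confirmed cases.** If a share g of 2b was admitted on an antibody result and all of them test positive, apparent Se = (1 − g) × 0.85 + g. For g = 0.10, 0.20 and 0.30 this is 0.865, 0.880 and 0.895 in 2b, and about 0.86 to 0.87 pooled with 2d. These are upper bounds, because not every earlier seroconverter need be positive on this ELISA more than a month after infection.

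**5. Would the data reveal it?** The 95% half-width at Se = 0.85 is 1.96 × √(0.85 × 0.15/n): 9.9 points at n = 50 and 7.0 points at n = 100. A result of 45/50 has an exact 95% interval of 0.78 to 0.97. Biases of this size would not stand out.

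**The case against.** **The article is condensed.** Analysis sets and case-report fields may sit in documents not shown. That holds for the database field and for subgroup rows. It does not dispose of the point: the article itself states both the entry rule and the classification of everyone in the infection groups as presumed seropositive, and the two together admit unproven cases as reference positives.

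**The clinical definition is strict.** Table 1 requires twelve named causes of rash, and other locally relevant ones, not to explain the picture. This stands, and the true non-case share may be below the assumed 30%. The article gives no figure either way.

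**The uncertainty is disclosed and the analysis is descriptive.** The article does use the word presumed and tests no hypothesis. But the cut-off is still estimated from these labels and then used.

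**Incorporation bias.** A reader might infer that admitting IgG seroconverters makes the validation circular, and that only NAAT-positive cases should count. The article does not support that. The index ELISA is not part of Table 2, IgM is not its analyte, and the ROC target is serostatus, for which documented seroconversion is direct evidence. A week-one serum paired with one at least 21 days later is also a demanding route, so such cases may be few. What remains is selection on the same or a related antibody response, which may raise apparent sensitivity after infection.

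**A wide combined range.** A reader might also join the two extremes and conclude that one assay could read anywhere from about 78% to 90%. That range sets opposite worst cases end to end within 2b alone and ignores the 50 vaccinees. On the same assumptions the pooled figures run only from about 81% to 87%.

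**Conclusion.** The concern holds for clinical-only cases. The plan's rules allow participants without laboratory proof to serve as reference positives, and nothing in the article separates them. Under the main assumptions the understatement of sensitivity is 2.4 to 7.2 points in group 2b (85% to 82.6–77.8%) and 1.2 to 3.6 points pooled with group 2d (85% to 83.8–81.4%). The pooled shift is within the sampling half-width of 7.0 points, but it is systematic and more samples would not remove it.

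The size rests entirely on assumed shares. If the Rwanda Biomedical Centre (RBC) records are nearly all laboratory-confirmed, the effect is negligible. The article reports 127 cases in Rwanda by 5 October 2025, and groups 2a and 2b need 60 people (60/127 = 47%). That could push recruitment towards every permitted route, but the article does not say how those cases were confirmed. The serological route is secondary, and the net direction of the two effects cannot be determined from the article. The point should be settled before the ROC analysis is run; it does not undermine the study as a whole.

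**What to change.** In the Statistical analysis plan, Part A:

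1. Define the infection positives for the primary ROC, AUC, cut-off and sensitivity as laboratory-confirmed cases by any Table 2 route.
2. Record the confirmation route of each group 2a and 2b participant from existing RBC records.
3. Report ELISA positivity in separate rows for NAAT-confirmed, serology-only and clinical-only participants.
4. Add the clinical-only participants back in a sensitivity analysis, and state whether the cut-off changes.

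Nobody is removed from the study and no test is added. The work is one data field and one analysis-set definition.

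The price is precision. If 40 of the 50 in group 2b remain (an assumed figure), the half-width at 85% sensitivity goes from 9.9 to 1.96 × √(0.1275/40) = 11.1 points. Pooled with the 50 vaccinees it goes from 7.0 to 1.96 × √(0.1275/90) = 7.4 points. If only 25 remained it would be 14.0 points in 2b. In that case the clinical-only share would be large enough that the pooled estimate could not be trusted without the separation.

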### Study interventions

#### Part A

All participants will provide informed consent using the latest Rwanda National Ethics Committee (RNEC) approved combined Study Information Booklet and Informed Consent Form (SIB/ICF) prior to commencement of any study procedures. Once informed written consent is obtained, the baseline assessments will be collected that include age, sex, region of residency, relevant medical history and national health number. A participant is enrolled at the point of sample provision. No formal follow-up of participants is planned as part of the study.

#### Safety

The study has minimal risk to participants. Phlebotomy carries a small risk of transient bruising and discomfort.

#### Participant samples

Each participant will be asked to provide a peripheral blood sample of up to 20mLs and a dried blood spot sample. Samples will be collected according to local standard operating procedures (SOPs).

#### Laboratory analysis

All laboratory procedures will be undertaken at the National Reference Lab in Kigali. Blood samples will undergo treatment to neutralise all infective agents and the removal of all human cells and genetic material before application to antibody-based assays in accordance with local SOPs.

All samples will undergo testing Mpox-specific IgG antibodies. The performance characteristics of the ELISA have been validated by the University of Birmingham and the United Kingdom Health Security Agency (UKHSA) during development of this ELISA. This ELISA will initially be validated and verified for use from known and presumed positive/negative study participants in Rwanda. This ELISA will then be employed as the reference standard against which performance of the prototype POC LFT will be measured.

### Sample storage

All samples will undergo pseudo-anonymisation at the study site before processing at laboratory facilities in accordance with SOPs. Participants will be given the option whether their samples can then be used anonymously for other vaccine research projects. They will also be asked whether anonymised samples could be used by commercial companies to develop other immunodiagnostic tests.

### Acceptability and feasibility assessment

A subsection of study participants will be invited to take part in semi-structured interviews/focus groups to receive feedback on the perceptions of antibody testing and disease outbreak management.

The following questions will be used as prompts to encourage full feedback from participants:

Question 1: In relation to engagement with the public when there is a disease outbreak, what do you feel works well, needs improvement, and how would you like to see this develop further?Question 2: In relation to taking biological samples to develop immunodiagnostics, what do you feel works well, needs improvement, and how would you like to see this develop further?Question 3: In relation to preparing to deploy additional vaccines for a disease outbreak, what do you feel works well, needs improvement, and how would you like to see this develop further?

### Sample size

#### Part A

The first stage of part A will involve validation of the University of Birmingham-developed multiplex ELISA evaluated on UK samples by University of Birmingham and UKHSA following Mpox infection with clade II virus and/or vaccination [25], using *N* = 50 samples each from groups 2b, 2d and group 3. The ELISA uses several Mpox proteins and shows excellent concordance with a multiplex bead assay developed by the UKHSA [25] on UK samples, with high sensitivity/specificity for identifying seropositivity. The performance of the ELISA will be evaluated on Rwandan participants with known status to evaluate the effect of factors such as ethnicity, nutritional status, chronic viral infection (e.g. HIV or hepatitis B) and pathogen factors such as clade Ib virus (the cause of the current outbreak) on test performance. The sub-group specific recruitment targets have therefore been expanded by 50% to accommodate potential confounders and improve the stability of estimates applied to this component of the study and the next steps in validation and assessment of clinical accuracy of novel POC LFTs. Once the performance of the Mpox ELISA is confirmed in serum, alternative sample matrices including plasma and dried blood spot (DBS) will be compared to IgG titres measured in serum in paired samples.

There is a lack of data on the current sero-prevalence of Mpox-specific immunity, which this study aims to address, meaning statistically driven power calculations are challenging. Sample sizes have been calculated according to Clinical & Laboratory Standards Institute standards and consistency with the design, setup and verification protocols used for new infectious diseases targets.

The sample size calculation has been derived from the assumption of 20% seroprevalence in the intended target-use population (high-risk individuals with no known past infection/vaccination), plus added assumptions of a 5% margin of error and a 10% allowance for the withdrawal of consent from any participants, missing data, and assay failures/invalid test results.

In total, *N* = 500 is required for this part of the study from the following study groups:

Group 1 (suspected exposure cohort): *n* = 330.Group 2a (infection within one-month of sampling): *n* = 10.Group 2b (infection over one-month before sampling): *n* = 50.Group 2c (vaccination within one-month of sampling): *n* = 10.Group 2d (vaccination over one-month before sampling): *n* = 50.Group 3 (no known past exposure to infection or vaccination): *n* = 50.

This sample size is sufficient for stability of estimates on POC LFT performance that will be deployed in parallel to the same study volunteers at the time of sampling.

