**Fig. 1 Fig1:**
[figure not shown]
Schematic presentation of the protocol

Part A will run in two stages, the first will validate an mpox-specific ELISA developed at University of Birmingham in a Rwandan laboratory with Rwandan samples of known clinical or vaccinated mpox status. The second stage will use this ELISA once successfully validated to perform a seroepidemiology study and evaluate the performance of a lateral flow test to identify the presence of mpox-specific antibody.

For Part B we aim to understand the vaccine cold-chain (VCC) operational needs for real-world impact of Mpox vaccines deployed for disease control.

Following rapid implementation of outbreak control measures including being the first in the region to administer mpox vaccines via a ring vaccination strategy [23], case numbers in Rwanda have remained low reaching 127 as of 5th October 2025, compared to 34,000 cases in the Democratic Republic of Congo [24]. Rwanda was selected as the study setting due to its epidemiological relevance and robust public health infrastructure. Rwanda neighbours both Uganda and DRC and we expect some overlap in background infections with cross reactivity with the ELISA, and we believe this will provide data applicable to the wider region.

The availability of meticulous vaccination and infection records enables the robust selection of well-defined mpox-case, MVA-BN vaccinated, and mpox-unexposed control groups. This structured approach, paired with the representative nature of the Rwandan Vaccine Cold Chain (managed by the Rwanda Biomedical Centre, RBC), ensures the study findings are highly applicable and generalizable to other African nations facing significant Mpox outbreaks.

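### The ELISA's between-clade question cannot be answered as planned: clade is confounded with country and laboratory, and the pooled ROC gives no infected-only sensitivity at the UK cut-off

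*Protocol article*

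**What the plan says.** All references are to the protocol article.

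- **Primary aims and objectives.** The ELISA is to be verified in a Rwandan population "with equivalent sensitivity for clade 1a Mpox compared with the clade IIb that it was established for". This is a statement about sensitivity between clades.
- **Sample size, Part A.** Stage 1 is to evaluate, beside ethnicity, nutrition and chronic viral infection, "pathogen factors such as clade Ib virus (the cause of the current outbreak) on test performance". The assay was previously "evaluated on UK samples by University of Birmingham and UKHSA following Mpox infection with clade II virus and/or vaccination". Stage 1 uses 50 "samples each from groups 2b, 2d and group 3", that is, past infection, past vaccination and controls.
- **Study design and setting.** The validation is to be done "in a Rwandan laboratory with Rwandan samples of known clinical or vaccinated mpox status".
- **Laboratory analysis.** "All laboratory procedures will be undertaken at the National Reference Lab in Kigali", after a local treatment step that inactivates the samples.
- **Statistical analysis plan, Part A.** One ROC curve sets vaccinated and infected participants together, as presumed seropositive, against those with no known infection or vaccination. "The best cut-off for identifying serostatus will be selected using this method based off the highest sensitivity and specificity". The analyses are described as mainly descriptive, without hypothesis testing.

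The objective names clade 1a and the sample-size section names clade Ib.

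**The concern.** The article describes no clade II sample tested in Kigali and no Rwandan sample tested in the UK. Between the UK cases and the Rwandan cases, clade changes together with population, laboratory, sample treatment and operator. A difference in sensitivity between the two sets of cases cannot be assigned to any one of these.

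The described analysis adds a second difficulty. Pooling 2b with 2d means that the ROC does not show how the assay performs in infected people alone. Re-selecting the cut-off in Rwanda means that the Rwandan and UK sensitivities are read at different thresholds.

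Two opposite errors are possible, depending on which cut-off is used. With a re-selected cut-off, a true loss for the outbreak clade could be restored on paper at the expense of specificity. With the UK cut-off kept, a plain laboratory or population shift could be taken for a clade loss. The ELISA then serves as the reference standard for the lateral flow test and as the instrument for the seroprevalence estimate, so an unclear result here carries forward.

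**Working it through.** **1. Which effects can be separated.** Take six cells: infected, vaccinated and negative, in the UK and in Rwanda. Let the mean log titre depend on a baseline, a country/laboratory shift, infection, vaccination and clade. That group 2b is all clade Ib is an assumption; the article gives no clade for individual participants.

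| Data used | Unknowns | Rank | Clade effect estimable? |
|---|---|---|---|
| Infected only, UK and Rwanda | 3 (baseline, country/laboratory, clade) | 2 | No: same column as country/laboratory |
| Rwanda only, three groups | 4 (baseline, infection, vaccination, clade) | 3 | No: same column as infection |
| All six cells | 5 | 5 | Yes, if the country/laboratory shift is the same in infected and vaccinated people |

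The first two rows do not depend on sample size. Raising the subgroup targets by 50%, as the sample-size section does to allow for confounders, leaves them unchanged.

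**2. If the UK cut-off is kept.** Assumptions, none of them given in the article: log10 titre SD 0.5 in positives, UK sensitivity 95%, no true clade effect. Then

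sensitivity in Rwanda = Φ(1.645 − shift/0.5).

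| Downward shift (log10) | Sensitivity | Apparent loss (points) |
|---|---|---|
| 0.1 | Φ(1.445) = 92.6% | 2.4 |
| 0.2 | Φ(1.245) = 89.3% | 5.7 |
| 0.3 | Φ(1.045) = 85.2% | 9.8 |

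The loss depends on the assumed UK sensitivity. In SD units, a shift of 0.25 SD costs 3.2 points if UK sensitivity is 95% and 5.1 points if it is 90%; a shift of 0.50 SD costs 7.6 and 11.7 points.

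**3. If the cut-off is re-selected.** If positives and controls shift alike, the AUC is unchanged, the chosen cut-off moves with them, and no sensitivity is lost. If instead only the cases lose 0.3 log10 through clade, a cut-off lowered by 0.3 log10 brings their sensitivity back to 95%, and the price appears in specificity only. The price cannot be computed, because the article gives no distribution for controls.

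**4. What pooling does.** Take the last row of step 2 as a true clade loss, with vaccinees still at 95%. With 50 in each group, pooled sensitivity at that cut-off is (50 × 85.2 + 50 × 95)/100 = 90.1%. A loss of 9.8 points in cases shows as 4.9.

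**5. Precision of a group-specific sensitivity.** With 45 of 50 positive (90%), the exact 95% interval is 78% to 97%. Even with separate reporting, a claim of equal sensitivity has to be modest.

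**6. What a vaccinated bridge would give.** The contrast is (Rwanda infected − UK infected) − (Rwanda vaccinated − UK vaccinated) on log10 titre. With SD 0.5 and an assumed 50 UK samples per cell, the 95% half-width is 1.96 × 0.5 × √(4/50) = 0.28 log10, or 10^0.28 ≈ 1.9-fold. The infected-only contrast has 1.96 × 0.5 × √(2/50) = 0.20 log10.

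In a simulation with 50 per cell, no clade effect and equal shifts of 0.25, 0.50 or 0.75 SD, the infected-only interval excluded zero in 24%, 71% or 96% of runs. The bridged interval did so in about 5%. The bridge removes the bias when its assumption holds, but its interval is as wide as the larger shifts in step 2.

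**The case against.** Four points can be made for the plan.

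- **Nothing says that a Rwanda–UK difference will be put down to clade.** The article lists clade Ib beside several host factors, calls the analysis descriptive, and speaks of verifying the assay in Rwandans. For that purpose, the combined effect of population, laboratory and clade is the relevant result. This stands: a reader might infer that the investigators will report a laboratory shift as a clade effect, but the text does not say so. It does not remove the point, because the objective is worded as a between-clade comparison and the described analysis does not supply one.
- **The apparent loss of 2.4 to 9.8 points assumes that the UK cut-off is retained, which the plan does not propose.** This stands too. The figure is conditional and does not predict what the plan as written would produce. Under the plan as written, the risk is the opposite one: a hidden loss.
- **The vaccinated group is not a ready-made control.** It is tempting to say that group 2d already separates clade from place. The documents do not support this. Group 2d admits any smallpox or MVA vaccination more than one month ago, at ages 5 to 80, so decades-old smallpox vaccination may be included. Whether the UK set has a vaccine-only arm of similar type and timing cannot be confirmed from the article. Host factors or background orthopoxvirus exposure may shift infected and vaccinated people differently. The bridge can only be supportive.
- **The full protocol or analysis plan may specify group-specific results or a bridging panel.** It may; a pooled ROC does not rule out separate reporting. But the article does state the objective, the ROC grouping and the choice of cut-off, and as stated these do not fit together.

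**Conclusion.** The concern holds in a limited form. On the design described, clade is fully confounded with country, population and laboratory. The pooled ROC with a re-selected cut-off gives no infected-only sensitivity at the UK threshold, so the between-clade objective cannot be answered as written. This conclusion is structural. It rests on the article's account of where the samples come from and on the inference that the Rwandan cases are clade Ib.

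The sizes are illustrations. If the UK cut-off were kept, a shift of 0.1 to 0.3 log10 would look like a loss of 2.4 to 9.8 points, given SD 0.5 log10 and UK sensitivity 95%. A re-selected cut-off could instead conceal a true loss of that order, and pooling with equal groups would halve it.

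The documents do not show that a false clade effect will be reported, nor that the vaccinated group is sufficient to isolate clade.

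**What to change.** 1. Report ELISA sensitivity in groups 2b and 2d separately, with specificity in group 3 and exact intervals, first at the unchanged UK cut-off and then at any cut-off re-selected in Rwanda.
2. State that a Rwanda-versus-UK difference in cases reflects clade, population and laboratory together and is not by itself a clade effect. Word the objective to match.
3. Reconcile clade 1a in the primary objectives with clade Ib in the sample-size section.
4. If the UK data hold comparable vaccine-only samples, add the infected-to-vaccinated difference of differences on log titre as a supportive analysis only. Restrict it to MVA vaccinees, adjust for time since infection or vaccination, and state both the equal-shift assumption and the expected interval (about ±0.28 log10 under the assumptions above; wider if the MVA restriction leaves fewer than 50 in 2d).

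Items 1 to 3 need no new participants or samples, only the UK cut-off, which the sponsor should hold as assay developer. The cost is a little more reporting and a more modest clade conclusion. Item 4 also needs the UK titres.
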